##### Endothelium-independent vasodilation: glyceryl trinitrate

2.7.10.3

Utilising the same machine settings, optimisation and placement of the ultrasound probes on the brachial and femoral arteries as those described above for the FMD assessment, endothelium-independent vasodilation was assessed following sublingual glyceryl trinitrate (GTN) administration. The reliability of GTN also has a high correlation (r = 0.84) [58]. Baseline recording of resting artery diameter, shear stress and blood flow velocity were conducted for 1 min. One sublingual dose (400 μg) of GTN was administered. Participants were also instructed to not swallow or talk for 1 min post-administration so that the medicine was absorbed into the blood stream across the mucosa, rather than being swallowed. Ultrasound measurements of artery diameter and blood flow velocity were recorded from 3 to 8 min post-administration. Analysis followed similar guidelines to that of FMD analysis.

##### Localised ischaemic handgrip exercise-induced vasodilation

2.7.10.4

A custom-built hand grip device was moved into position with the participants arm supported in a comfortable position. Ischaemic handgrip exercise provides an index of maximal diameter and blood flow in the brachial artery [60]. This followed the same protocol of the FMD procedure in the arm. In addition, participants were instructed to handgrip to a metronome for the middle 3 min of cuff inflation (25 isotonic contractions per minute with the weight of the handgrip machine set at 1.25 kg). Peak artery FMD (absolute and %), blood flow, shear stress, time to peak and artery diameter, pre-post cuff deflation were analysed.

##### Peripheral arterial stiffness and velocity

2.7.10.5

Peripheral artery stiffness and pulse wave velocity were assessed via SphygmoCor (SphygmoCor, AtCor Medical, Sydney, Australia. Model Xcel. Software version 7.01 S). The validity and reliability of the SphygmoCor Xcel has previously been investigated and described [61]. Pulse wave analysis (PWA) is assessed with participants instructed to lay flat with their eyes closed. A brachial cuff is placed on the left arm and three automated cuff inflations are acquired at 60s intervals over 5 min with an additional inflation at the end of the 5 min to capture 10s PWA of the brachial artery (AIx@75). In this study PWA was used to assess central blood pressure (pressure at the level of the aorta) and the stiffness of the brachial artery. Blood pressure was also derived at each of the three measurements and the average DBP and SBP was used for pulse wave velocity (PWV; Supplementary Fig. 4) assessment.

Carotid-femoral PWV indicates arterial stiffness, calculated by measuring the speed of the pulse travelling down the arteries. The brachial cuff was removed, and a femoral cuff was placed around the upper right thigh, as close to the groin as possible, with the lead on the middle lateral side of the leg pointing towards the head. While the right thigh was flexed, participants located their femoral crease with their index finger and the distance between the anterior femoral crease and proximal superior part of the femoral cuff was noted in the system. The right carotid pulse was located and marked at its most prominent point along with marking the sternal notch. The distance between the carotid pulse-sternal notch and the sternal notch-proximal superior femoral cuff was also recorded and noted. These indicate the PWV distance between the carotid and femoral pulses. The system was set to a capture time of 10 s, subtraction method was used, and cuff/tonometer sync was turned off. The femoral cuff was inflated around the right thigh to a pressure of 180 mmHg to capture the femoral pulse. Simultaneously, a tonometer was held on the carotid pulse marked to capture the carotid pulse. The PWV was automatically captured when ~10 corresponding carotid and femoral pulses were higher than the quality threshold. A second measure was repeated to ensure consistent results and if the difference between the first and second reading was >0.5 m/s then a third reading was performed.

#### Cardiac measures

2.7.11

##### Cardiac MRI

2.7.11.1

Measures of left (LV) and right (RV) ventricular morphology were assess using a 1.5T MRI machine (Magnetom Espree, Siemens, Erlangen, Germany) in a 30 min scan. The reliability of CMR preformed 7 days apart has reported high correlations for LV mass (r = 0.99), EDV (r = 0.99), ESV (r = 0.93) and EF (r = 0.94) with non-significant differences between timepoints (*P* > 0.05) [62]. Participants were scanned in the supine position with a posterior phased array spine coil and anterior flexible phased array body surface coil. Multi-plane breath-hold using steady-state free procession (TrueFISP) localisers were acquired to obtain standard cardiac imaging planes. For all sequences, the breath-hold times varied between 5 and 10s, depending on the participants HR. To evaluate functional parameters, breath-hold TrueFISP cine images were acquired using a retrograde ECG trigger covering the whole R-R interval. Images of the LV and RV were acquired in short axis plane, perpendicular to the ventricular septum. Between 10 and 12 slices were acquired (6 mm slices/4 mm gap, FoV 320–350 mm, TR = 37.68, TE = 1.29 flip angle 70–80 deg, resolution 256 × 166, BW 930). Cine images of the four-chamber and LV outflow tract were also acquired (6 mm slices, FoV 300–330 mm, TR = 38.28, TE = 1.32, flip angle 70–80 deg, resolution 224 × 224, BW930). All cardiac MRI analysis was performed using specialized software (ARGUS, Siemens). Analyses were independently repeated and confirmed by an experienced cardiologist, who was blinded to twin zygosity and pairing. To assess LV morphology, systemic and pulmonary outflow tracts were auto-segmented in individual slices on cine images and then manually adjusted where necessary. Short axis cine loops were inspected to define LV end-diastolic volume (EDV) and end-systolic volume (ESV) frames. The mitral valve markers were automatically displayed on two- and four-chamber cine views but could be manually manipulated if inconsistent tracking occurred throughout the slices. However manual placement was required for markers of the tricuspid valve in RV analysis. The basal LV and RV slices were taken as the first slice below the level of the mitral valve and tricuspid valve, respectively. Therefore volumes above the aortic valve and those surrounding the thin myocardial wall in the mitral valve and tricuspid valve plane were excluded from analysis. Endocardial and epicardial LV borders were automatically contoured (but could be manually manipulated if required), including the septum but excluding the papillary muscles which were added to LV EDV and LV ESV in accordance with the methods described previously [8,63]. LV mass was calculated by summing the LV EDV within the epi- and endo-cardial borders of the short-axis slices, multiplying the myocardial tissue volume by its specific density (1.05 g cm−3). The LV EDV and LV ESV were utilised to ascertain stroke volume, ejection fraction and cardiac output. The RV endocardium was manually traced on each short axis frame. Data was validated by checking that systemic flow, pulmonary flow, LV and RV stroke volume were all within 5% of each other. Any deviations resulted in re-analysis and, if required, review by a cardiologist. To facilitate valid comparison to previously obtained echocardiographic data, a representative measure of LV internal cavity dimension during diastole (LVIDd) and systole (LVIDs), as well as interventricular septum and posterior wall thickness were determined from the short-axis view between the LV outflow tract and papillary muscle slice. Any error >2% resulted in both measurements being re-measured at a later date by a blinded reviewer. For assessment of RV morphology, instructions for tracing the endo- and epicardial borders were taken from the methodology described previously [6]. To overcome difficulties in determining the RV in the basal two slices, short axis cine loops were inspected for end-systole, which was defined as the frame with the smallest ventricular cavity. In the most basal end-diastolic slice, a RV contour was drawn only if it was visible for a minimum of three-phases in diastole, whereas the visible RV contour was always traced in the most basal end-systolic slice. RV mass was determined by subtracting the volumes between the epi- and endocardial borders, multiplying by slice thickness and myocardial specific density and summing the slices of this area during end-diastole and end-systole. As the epicardial border overlapped both the septal part of the endocardial border and at the valve planes, RV mass was calculated from the RV lateral wall only. RV EDV and ESV, as well as derived stroke volume, ejection fraction and cardiac output were calculated.

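### As worded, the right-ventricular mass rule leaves out the 4 mm slice gap and can be read as adding two cardiac phases, so it does not return lateral-wall mass in grams

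*Protocol article*

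**What the plan says.** All of the relevant text is in the protocol article, section 2.7.11.1 (Cardiac MRI).

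- Acquisition of the short-axis stack: "Between 10 and 12 slices were acquired (6 mm slices/4 mm gap".
- Starting quantity for RV mass: "RV mass was determined by subtracting the volumes between the epi- and endocardial borders".
- Next step for RV mass: "multiplying by slice thickness and myocardial specific density and summing the slices of this area during end-diastole and end-systole".
- Region: "RV mass was calculated from the RV lateral wall only".
- Density, given in the left-ventricular (LV) sentence: "multiplying the myocardial tissue volume by its specific density (1.05 g cm−3".
- Software and source of the tracing rules: "All cardiac MRI analysis was performed using specialized software (ARGUS, Siemens" and, for the RV, "instructions for tracing the endo- and epicardial borders were taken from the methodology described previously [6".
- Quality check: "Data was validated by checking that systemic flow, pulmonary flow, LV and RV stroke volume were all within 5% of each other".

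Section 3 (Planned statistical analysis) defines the training response as the post value minus the pre value and reports group means with confidence intervals. Section 3.2 (Sample size and power) lists cardiac adaptation among the primary outcome measures, without naming RV mass.

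**The concern.** A mass from a short-axis stack is a sum of discs. Each disc is a wall area multiplied by the length of ventricle that the slice represents, and the total is multiplied by tissue density. The RV rule departs from this in three ways.

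1. The article treats slice and gap as separate lengths. Multiplying by slice thickness alone, with no mention of the gap, leaves 4 of every 10 mm of wall uncounted.
2. Summing over end-diastole and end-systole can be read as putting the same muscle into one total twice.
3. The rule multiplies volumes by a thickness and then calls the quantity an area. Volume times length times density has units of gram-centimetres, not grams.

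At stake are RV mass in grams and its post-minus-pre change, which would be reported with means and confidence intervals on the wrong scale. A reader could neither reproduce the figure nor set it beside an RV mass from another study. The stated quality check compares flows and stroke volumes and does not include mass.

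**Working it through.** The article gives no RV mass in grams, so there is no figure to reproduce. The check compares readings of the rule.

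**Inputs from section 2.7.11.1.** Thickness t = 6 mm; gap g = 4 mm; spacing t + g = 10 mm; density 1.05 g/cm³; 10 to 12 slices.

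**Assumptions.** Wall area is taken as equal across slices. The ratio r of traced end-systolic to end-diastolic wall volume is 1.0 if muscle volume is conserved, and is varied from 0.8 to 1.1.

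**Reference.** Mass in one phase = 1.05 × Σ(epicardial area − endocardial area) × 10 mm, set to 1.00.

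**Readings, relative to the reference.**

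| Length per slice | Use of phases | Factor | At r = 1 | r from 0.8 to 1.1 |
|---|---|---|---|---|
| 10 mm | one phase | 10/10 | 1.00 | – |
| 6 mm | one phase | 6/10 | 0.60 | – |
| 6 mm | both added | 0.6 × (1 + r) | 1.20 | 1.08 to 1.26 |
| 10 mm | both added | 1 + r | 2.00 | 1.80 to 2.10 |

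Averaging the phases at 6 mm gives 0.6 × (1 + r)/2, which is again 0.60 at r = 1. Omitting the gap and adding the phases work in opposite directions. They cancel only if 0.6 × (1 + r) = 1, that is r = 2/3.

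**In grams.** Take an assumed wall area of 3 cm² per slice, chosen only for illustration.

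- 10 slices, reference: 10 × 3 × 1.0 × 1.05 = 31.5 g. The other three readings give 18.9 g (6 mm, one phase), 37.8 g (6 mm, both added) and 63.0 g (10 mm, both added).
- 12 slices, reference: 12 × 3 × 1.0 × 1.05 = 37.8 g. The other three give 22.7 g, 45.4 g and 75.6 g.

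With a constant factor, a change scales in the same way: a true change of 1 g would appear as 0.60, 1.20 or 2.00 g.

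**What a constant factor k leaves unchanged.** The intraclass correlation is a ratio of variances, so k² cancels. In 200 simulated pairs it was 0.4217 at k = 1, 1.2 and 0.6. The A, C and E proportions are likewise ratios. Percent change is unchanged because k cancels, and the sign of a change is unchanged because k > 0. Response rates and concordances in section 3 are based on change above zero, so they are unchanged too.

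**Where the factor need not be constant.** If the phases were added, the factor contains r, which can differ between scans. The article gives different rules for the most basal slice: at end-diastole a contour depends on visibility over at least three phases, whereas at end-systole any visible contour is traced. The invariance is then no longer exact.

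**The case against.** The strongest reply is that this is condensed methods prose read as if it were a formula. The RV sentence gives no number; 6 mm comes from the acquisition line. The analysis was done in ARGUS, whose handling of the gap is not described, and RV tracing follows an earlier publication that is not at hand. Summing during both phases also fits a separate per-slice sum in each phase. The LV sentence is loose as well: read literally, it sums a cavity volume. If the length used was the 10 mm spacing and each phase gave its own mass, the factor is 1.00 and only the wording is at fault.

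The quality check offers some further support. If the flows were measured independently of the short-axis stack, which the article does not say, a software-wide failure to count the gap would put stroke volumes about 40% low and breach the 5% tolerance. That makes a gap-blind stack less likely. It would not reveal an error confined to the mass calculation or to adding phases.

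Most of this stands, and it limits what can be claimed. Three stronger inferences are tempting and are not supported:

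- **That the recorded RV masses are wrong, for example 40% too low.** The article does not show which length was applied or whether the phases were added.
- **That the heritability results are damaged.** A constant factor does not touch them.
- **That an LV-to-RV comparison is spoiled.** None is planned, and the two masses differ by design because the RV figure covers the lateral wall only.

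What does not stand is that nothing needs correcting. The article states a rule and has itself defined the slice and the gap as separate lengths. In those terms, no one-phase, averaged or separately reported reading gives the full mass.

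**Conclusion.** The point holds as an error in the stated rule, not as a proven error in the data. Followed as worded, the rule gives 0.60 of the RV lateral-wall mass in one phase, or about 1.20 (1.08 to 1.26) if the phases are added. If the length was really the spacing but the phases were added, the factor is about 2.0 (1.80 to 2.10). A correct mass requires both that slice thickness was meant as the 10 mm spacing and that the phases were not added. The document fixes neither, so it fixes neither the size nor the direction of any actual error.

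The consequence is confined to RV mass and its change in absolute grams, with their group means and confidence intervals. The primary twin analysis is unaffected by a constant factor. The figures rest on equal wall area across slices and on the assumed range for r.

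**What to change.** 1. Restate the rule: RV mass = sum over slices of (epicardial area − endocardial area) × slice spacing (thickness plus gap, 10 mm) × 1.05 g/cm³, for the lateral wall.
2. State how the phases are used: one named phase, the mean of the two, or each reported separately, but never their sum. The choice among the first three is the investigators'.
3. Verify from the ARGUS settings or output which length per slice was applied and how the phases entered.
4. Recompute RV mass from the stored contours only if the gap was omitted or the phases were added. Otherwise correct the text alone.

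The cost is one corrected sentence, one check of the software and, at most, a recalculation from existing contours. No new scans are needed.

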
##### Echocardiography

2.7.11.2

All echocardiographic images were acquired on a commercially available ultrasound system (EPIQ-7, Koninklijke Philips N.V., Philips Electronics Australia Limited, New South Wales, Australia) using a 1–5 MHz phased array transducer. A highly experienced qualified sonographer performed all assessments and was blinded to exercise group allocation. Subjects lay in the left lateral decubitus position and image acquisition followed standard adult transthoracic echocardiographic protocol [64]. Two-dimensional images of the parasternal long-axis (PLAX) and the parasternal short axis (PSAX) views were obtained according to the American Society of Echocardiography recommendations (ASE [[64], [65], [66]]). Images of the ventricles and atria were obtained from an apical four-chamber (A4C) view, with the walls and septa of each chamber achieved for assessment of size and function [64]. LVIDd, LVIDs, septal and posterior wall thicknesses were determined from the PLAX view, while left atrial (LA) and LV chamber volumes were determined from the A4C and apical two-chamber (A2C) views. The function of the mitral, tricuspid and aortic valves were also obtained in the apical view using colour and spectral Doppler. Diastolic function of mitral inflow, and annular tissue Doppler of medial and lateral mitral annulus for diastolic function, was assessed using pulsed Doppler and tissue Doppler in the A4C view [66]. With the participant laying supine with knees bent, the subcostal view was obtained by pressing the transducer into the area just inferior to the sternal xiphoid process. This view was used to investigate the inferior vena cava diameter during expiration and normal function of the central venous pressure (should collapse when participants take a rapid “sniff” in), and the presence of any atrial septal defects (i.e. patent foramen ovale). The suprasternal view was also obtained in the supine position with the patients head tilted backwards and the transducer placed in the sternal notch pointed inferiorly to view the long axis of the aortic arch. The aforementioned imaging windows were optimised prior to acquisition using 2D imaging optimisation techniques described in the ASE guidelines (i.e. greyscale maps, dynamic range, transmit frequency, harmonic imaging, sector size and depth). Standard imaging techniques of 2D spectral, colour and tissue Doppler were also applied as described previously [65,67]. Myocardial strain and 3D volumes and masses were also derived. Strain and strain rate measures the actual degree of myocardial deformation (cardiac mechanics and systolic ventricular function) independent of the adjacent myocardial segments and can therefore differentiate the active and passive contraction of the myocardium [67]. Strain and strain rate was derived from 2D speckle tracking echocardiography which is an angle independent method for strain and strain rate analysis. Cardiac mechanics were assessed in the three myocardial axes related to strain; longitudinal, circumferential and radial. Apical imaging was used to assess longitudinal strain, circumferential and radial strain from the short axis view. From this, global longitudinal strain was determined and a bull's eye plot was produced. Minimum frame rates for high-quality imaging acquisition (>60 frames per second) were established [65]. Three-dimensional imaging was used to assess LV and LA volumes, mass and function. The A4C was optimised with the gain and compression set at mid ranges as previously recommended [68]. The focus, time gain compensation and field of view were also optimised to maximise temporal and spatial resolution, and volume rate. Once the operator was satisfied with the image quality, then the 3D image was captured. Cine loops of all images were recorded to USB hard drive in a raw DICOM format and native data and analysed offline again by a single experienced blinded observer.

## Planned statistical analysis

3

Statistical analyses are to be performed with SPSS 20.0 (IBM Australia Ltd, New South Wales, Australia) and STATA 11 software (StataCorp, College Station, Texas). All data will be reported as group means with confidence intervals, with default statistical significance assumed at *P* < 0.05. Cross-sectional results for each outcome measure refer to baseline entry (week 0) data. Response to training data is post minus pre for END and RES training. Normality of groups (MZ and DZ) will be assessed via Shapiro-Wilk test of normality where normality of spread is assumed at *P* > 0.05. Between-group (MZ vs DZ) differences will be assessed with the conservative non-parametric Mann-Whitney *U* test and regression models including the single covariate zygosity (MZ/DZ), fitted using a generalised estimating equation (GEE) approach to account for correlation of twins within-pairs. The effect of the exercise interventions on each outcome measure will be assessed using a linear mixed models approach.

The primary objective of the current study is to estimate the MZ and DZ correlations and the variance components A, C and E for each outcome measure cross-sectionally, and in response to exercise training (END and RES). In STATA mixed models effects will calculate intraclass correlation coefficients (r) for MZ and DZ twin pairs. Covariates to be adjusted for (e.g. sex, fat-free mass, VO_2max_, baseline data) will depend on the primary outcome measure. The subsequent rMZ and rDZ, and their respective P-values and 95% confidence intervals will be presented. Differences between intraclass correlations (rMZ vs rDZ) will be assessed using the likelihood-ratio test in STATA to compare mixed effects models constraining covariances for MZ and DZ pairs to be equal with models allowing different covariances for MZ and DZ pairs [69]. If the model allowing different MZ and DZ covariances are significantly better, and rMZ are significantly different to rDZ, A, C and E will then be calculated from the estimates of the DZ covariance and the additional MZ covariance, and confidence intervals for A, C and E will be estimated using the delta method. When rMZ and rDZ are not significantly different then a single model that includes all twin pairs but constrains the covariance to be equal for MZ and DZ pairs will be used in STATA to calculate C and E components only, and their respective 95% confidence intervals. An additional model which estimates covariance for MZ twins but fixes the DZ covariance to be zero will test if the estimated correlations suggest that the equal environments assumption has been violated.

Secondary objectives of this study will be addressed using the individual change with training (END and RES) results for each outcome measure. Response rates for each modality can be derived as a percentage of positive responses (>0) and compared against one another by a Z-test. Concordances can be derived as the percentage of individuals who positively respond to both exercise training modalities (Supplementary Fig. 5). In a similar way to the correlation analyses, within-twin pair concordances for MZ and DZ can be derived for each exercise intervention and compared to each other.

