### Participant recruitment

2.3

Healthy, same-sex DZ and MZ twin pairs, between the ages of 16–40yrs, were recruited to participate in the study. Recruitment started in September 2016 and was facilitated by Twins Research Australia (formerly Australian Twin Registry [33]). Twin pairs in the Metropolitan Perth-based region were sent emails, newsletters and conventional mail regarding participation in the study. Other recruitment methods included advertising in local and Perth-based newspapers, online and social media recruiting, The University of Western Australia (UWA) email lists, flyers around UWA and nearby establishments, and word of mouth. Baseline demographic data is displayed in Table 1, and a participant flow chart in Fig. 1.

**Table 1 tbl1:** Baseline characteristics of participants enrolled in the study.

		Monozygotic (MZ)	Dizygotic (DZ)
		n = 62 (31 twin pairs, 18 F, 13 M)	n = 28 (14 twin pairs, 10 F, 4 M)
		Mean (SD)	Mean (SD)
Age (yrs)	F	24.2 (5.0)	23.8 (4.2)
	M	28.0 (5.9)	22.9 (5.3)
	Total	26.2 (6.1)	23.5 (4.5)
Height (cm)	F	170.2 (4.0)	168.6 (5.9)
	M	180.8 (4.5)	178.0 (6.6)
	Total	174.5 (6.5)	171.8 (7.5)
Weight (kg)	F	67.0 (19.6)	59.3 (9.4)
	M	81.0 (12.8)	69.1 (11.3)
	Total	74.9 (18.9)	62.6 (10.9)
BMI (kg/m^2^)	F	23.0 (6.1)	20.9 (2.8)
	M	24.7 (3.6)	21.7 (2.7)
	Total	24.4 (5.3)	21.1 (2.9)

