### Sample size and power

3.2

Power analysis is based on our primary outcome measures which are highly specialized and sensitive; vascular function (FMD), cardiac and cerebrovascular adaptation. Our cardiac publications [6,8,9] have reported significant effects in fewer subjects (n = 10 and n = 13 per group) than we recruited in the present study; we observed highly significant differences utilising highly sensitive MRI. Regarding cerebral measures, previous publications and our pilot work demonstrate that cerebral blood flow is increased in older individuals (n = 9, 65–78 yrs) by 10% after intervention. Our previous twin study publications in a paediatric population [24,31] cross-sectionally revealed FMD correlations of 0.6 and 0.38 in MZ and DZ twin pairs, respectively, in a smaller sample size of 22 (11 pairs) per group [24]. In addition, this study applied an exercise intervention (8 weeks) shorter than the current study (12 weeks), and produced correlations of 0.74 and 0.37 for FMD responses in MZ and DZ groups (n = 24–6 pairs per group) [31]. A power analysis (G*Power v3.1.2), performed using the predicted correlations for rMZ = 0.80 and rDZ = 0.30, assuming alpha = 0.05, indicates that a sample size of 23 individuals in each group provides 80% power.

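### The supportive MZ v DZ mean comparison is fixed as unadjusted, although the two groups differ in sex mix and age; add both to the GEE

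*Protocol article*

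**What the plan says.** Section 3 (Planned statistical analysis) names two methods for this contrast. The first is rank-based: "Between-group (MZ vs DZ) differences will be assessed with the conservative non-parametric Mann-Whitney" U test. The second is "regression models including the single covariate zygosity (MZ/DZ), fitted using a generalised estimating equation (GEE) approach", with GEE used to handle the correlation of twins within a pair. Calling zygosity the single covariate settles the content of the model, so this is not a detail left for a fuller plan.

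The next part of section 3 does allow adjustment: "Covariates to be adjusted for (e.g. sex, fat-free mass, VO_2max_, baseline data) will depend on the primary outcome measure". That sentence belongs to the mixed models that give rMZ and rDZ. Nothing extends it to the comparison of means, and age is not among its examples.

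On composition, section 2.3 states: "Healthy, same-sex DZ and MZ twin pairs, between the ages of 16–40yrs, were recruited". Table 1 heads its columns "n = 62 (31 twin pairs, 18 F, 13 M") for MZ and "n = 28 (14 twin pairs, 10 F, 4 M") for DZ, and gives age, height, weight and BMI by sex.

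**The concern.** Zygosity is a characteristic that the pairs bring with them, so no feature of the design balances sex or age between MZ and DZ. Both are properties of the pair: the twins are same-sex and of the same age. GEE corrects the standard error for two twins resembling each other, but it does nothing about MZ pairs differing from DZ pairs in sex and age.

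Two things follow for an outcome that depends strongly on sex. Part of the estimated zygosity difference is only the sex mix, and the between-sex variance stays in the residual and widens the interval. Several planned week 0 outcomes plausibly behave this way (1RM strength, VO2max, lean mass, cardiac mass and volumes), although the article gives sex-specific figures only for age and body size. At stake is whether a reader can trust a reported similarity or difference in MZ and DZ means, which is background to reading rMZ against rDZ.

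**Working it through.** **The plan's own figure.** The only sample-size statement (section 3.2) concerns correlations: it "indicates that a sample size of 23 individuals in each group provides 80% power" for rMZ = 0.80 and rDZ = 0.30. By Fisher's z, n = 3 + 2[(z_α + z_β)/(atanh 0.80 − atanh 0.30)]². This gives 22.86, so 23, one-sided, and 28.2, so 29, two-sided. The figure reproduces one-sided only. It says nothing about means, and the present point does not rest on it.

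**Inputs from Table 1.**
- Male pairs: 13/31 = 0.419 (MZ) and 4/14 = 0.286 (DZ), a difference of 0.134.
- Age: 26.2 v 23.5 years overall; men 28.0 v 22.9; women 24.2 v 23.8.
- Height, F and M, mean (SD): MZ 170.2 (4.0) and 180.8 (4.5); DZ 168.6 (5.9) and 178.0 (6.6).

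With pairs as units, the imbalances are not significant (sex: Fisher p = 0.51; age: Welch p = 0.11).

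**Worked example: height.** Some Table 1 totals differ from the sex-weighted means, so I rebuilt the totals from the sex rows.
- MZ mean: (18 × 170.2 + 13 × 180.8)/31 = 174.65. DZ mean: (10 × 168.6 + 4 × 178.0)/14 = 171.29. Crude difference 3.36 cm. (The stated totals give 174.5 − 171.8 = 2.7 cm.)
- Within sex, the differences are 1.6 cm (F) and 2.8 cm (M). Weights n_MZ·n_DZ/(n_MZ + n_DZ) are 18 × 10/28 = 6.43 and 13 × 4/17 = 3.06. Sex-adjusted difference: (6.43 × 1.6 + 3.06 × 2.8)/9.49 = 1.99 cm.
- Sex mix therefore accounts for 3.36 − 1.99 = 1.37 cm, or 41% of the crude difference.
- Standard errors at pair level, taking within-pair correlation as 1: crude √(6.70²/31 + 7.34²/14) = 2.30 cm; adjusted 1.82 cm; ratio 1.27.

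The same calculation for weight moves the difference from 10.8 to 9.1 kg and the SE from 4.36 to 4.30. For BMI the difference moves from 2.58 to 2.39 and the SE from 1.19 to 1.27, so precision is not improved.

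**General size.** Let g be the male-female gap in within-sex SDs and p = 17/45 the overall male share. The shift is 0.134g. The SE ratio, unadjusted to sex-adjusted, is √(1 + p(1 − p)g²) × √(1 − R²), where R² = 0.134² × (31 × 14/45²)/[p(1 − p)] = 0.016.

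| g (assumed) | shift (SD) | SE ratio |
|---|---|---|
| 0.5 | 0.07 | 1.02 |
| 1.0 | 0.13 | 1.10 |
| 1.5 | 0.20 | 1.23 |
| 2.0 | 0.27 | 1.38 |
| 2.5 | 0.33 | 1.56 |

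**Simulation.** Settings: 31 and 14 pairs with the actual sex counts, ages drawn from Table 1, twin correlation 0.6 (assumed), robust SE on pair means, two-sided 5% test, zygosity only against zygosity + sex + age.
- g = 1.5: mean SE 0.363 v 0.293, ratio 1.24.
- g = 1.5, men scoring higher, true difference 0.7 SD (assumed): rejection unadjusted 24% if DZ is higher and 73% if MZ is higher; adjusted 66% either way. The unadjusted average is (24 + 73)/2 ≈ 49%.
- g = 0.8: the unadjusted figures are 49% and 75%, average 62%, against about 66% adjusted.
- g = 0.3 (uncorrected robust SE): about 69% on average under both models.
- No true difference, g = 1.5, no age effect: 5% unadjusted; 7% to 8% adjusted with an uncorrected robust SE.
- No true difference, g = 1.5, assumed age slope 0.3 SD per 5 years: about 10% unadjusted, 6% to 7% adjusted.
- Sex and age irrelevant: sampling SD 0.287 unadjusted, 0.297 adjusted, about 3% more.

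**The case against.** The best defence is one of purpose. No objective (section 2.1) or hypothesis (section 2.2) concerns a difference in MZ and DZ means. The comparison stands beside the normality check and reads as a check on whether the groups are comparable. For that, an unadjusted contrast of the groups as enrolled is legitimate, and adjustment answers a different question. This stands, and it is why the unadjusted means should be kept as description. It does not justify making an unadjusted model the only regression, when sex is already named as a covariate for the correlation models.

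The imbalance is also modest, and the age gap comes mainly from men, with only four DZ male pairs. That limits how well the adjusted model can be estimated. Non-significance does not remove the shift in the sample enrolled.

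A reader might infer four stronger things that the document does not support.
- **That the heritability results are biased.** The rMZ, rDZ and A/C/E models are separate and may adjust for sex.
- **That MZ is always flattered.** The direction follows the sex gap and reverses where women score higher.
- **That sex mix alone inflates false positives.** With the sex counts fixed, the over-wide SE offsets the shift and rejection stays near 5%. Inflation appeared only with an assumed age slope, and the article gives none.
- **That planned power is lost.** The plan posits no mean difference; the 0.7 SD effect is an illustration.

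**Conclusion.** The point holds as an improvement to a supportive analysis. As written, the MZ v DZ mean comparison has no adjusted version, and the groups differ in two collected pair-level factors. For strongly sex-dependent week 0 outcomes, the estimate carries a shift of 0.134 times the sex gap. Its SE is about 25% too wide at a gap of 1.5 within-sex SD. That gap is an assumption: in Table 1, DZ height shows about 1.5 SD and MZ height about 2.5, while weight shows 0.8 to 1.0. Height itself is a descriptor and not a listed experimental measure, so it illustrates the mechanism only.

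The effect is small for weakly sex-dependent outcomes. It is unknown for END and RES responses, because no sex gap in change scores is documented. The contribution of age cannot be sized without a slope.

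**What to change.** In section 3, replace the zygosity-only GEE with one containing zygosity, sex and age, and specify a small-sample correction to the robust standard error because there are only 14 DZ pairs. Report that estimate and its interval as the inferential MZ v DZ result for week 0 values and for END and RES responses. State that the unadjusted means and the Mann-Whitney test, which takes no covariates, are descriptive.

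The cost is one sentence and no new data, since age and sex are already recorded. The downside is two more parameters with 45 pairs, which raises the sampling SD by about 3% where neither factor matters. Without the small-sample correction, the adjusted test would reject slightly too often, so the two changes should be made together.
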